We chose to use an ITS instead of a randomized controlled trial because in the context of community-wide infrastructure projects, randomized trials are infeasible and may come with additional equity and ethical concerns, regardless of the fact that health effects specifically attributable to sanitation are variable across trials (25,26). To address concerns that may arise in the absence of a randomized controlled trial, we will include a minimum of 10 additional households from a neighboring community that has existing adequate sanitation and 10 more comparison households with poor sanitation that will not be connected to the intervention until after the conclusion of this study. These 20 comparison sites will allow estimates of (1) background levels of fecal microbes in sample matrices and (2) the influence of non-intervention-related factors (e.g., flooding) on the presence and quantity of sanitation-related microbes. The comparison sites, along with the fact that we are sampling at multiple time points before and after the intervention, will allow us to account for temporal and spatial variation in microbial density.

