### Sample Size Calculations

We calculated a sample size for our primary outcome using a time series regression appropriate for an ITS design. Here we calculate the number of households, *n*, that will be followed longitudinally across the six sampling time points, *t*, (three before and three after the intervention) to detect a meaningful change in soil *E. coli* concentrations with 80% power at a 5% significance level. Equation 1 calculates the crude number of households, *m*, needed before accounting for clustering (27).

Equation 1
$$m=\frac{2{\left(z_{\alpha }+z_{Q}\right)}^{2}\sigma^{2}\left(1-\rho_{1}\right)}{ts_{x}^{2}d^{2}}$$

In this equation the term *σ*^*2*^ captures the total variability in *E. coli* concentrations across all locations and time points, while *s*
^*2*^ accounts for the variability in repeated measurements within the same location. The intraclass correlation coefficient, ρ_1_ reflects how similar those repeated measures are over time for a given household. Finally, the effect size, *d*, is the expected change in log-transformed *E. coli* concentrations in soil attributable to the sanitation intervention.

To estimate the values used in this calculation, we used log-transformed concentrations of *E. coli* ybbW in soil samples based on preliminary data from soil samples collected in Hale County in 2023 (22). For sample size calculations, we assumed that *E. coli* ybbW in soil could serve as a proxy for culturable *E. coli* in soil, based on a moderate positive correlation observed between the two measures in soil samples (Spearman’s ρ = 0.54, *p* = 0.03). The total variance, *σ*^*2*^, was calculated as 5.2 log (copies/gram)^2^ based on all available soil samples. The within-household variance, *s*
^*2*^, was estimated as 4.3 log (copies/gram)^2^ from a mixed-effects model including a random intercept for location. The intraclass correlation coefficient, *ρ*_1_, which reflects the correlation of repeated measurements within a single location over time, was estimated to be 0.16. The effect size, *d*, was defined as a 0.45-log (copies/gram) reduction in soil concentrations, which corresponds to 20% of the standard deviation of log-transformed values from the pilot data. We selected this threshold to reflect a small but meaningful reduction in environmental fecal contamination. Using these inputs and *t* = 6 time points per household, we calculated an intermediate value of *m* = 13 households needed before adjusting for clustering.

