Equation 2
$$n=m*\left(\left(1+\rho_{2}\right)*\left(\text{k}-1\right)\right)$$

To account for clustering of soil samples within sites, we applied Equation 2 (27). The intracluster correlation coefficient, ρ_2_, used in this adjustment was estimated as 0.17 from a model based on the preliminary data set that included random intercepts for both location and sampling date. We define *k* as the number of observations within each visit—in this case, the total number of soil samples collected for each soil type (impacted versus unimpacted) —which was set to *k* = 3. This adjustment yielded a final, design-corrected sample size of approximately *n* = 30 households needed to detect the specified effect size with 80% power at the 5% significance level.

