### Soil Sample Collection

At each of the six time points, three soil samples will be collected from an area thought to be impacted by failing sanitation, as identified by the participant living in the household. If the household is relying on a cesspool or straight pipe, a sample will be collected directly at the point of impact by collecting the top layer of the receiving soil, with additional samples collected one foot away and three feet away from the point of impact. If the household is relying on a septic tank with a septic field, soil samples will be collected from three randomly selected locations overlaying the septic field. Impacted soil samples will not be collected at the 10 households with existing adequate sanitation services, which, by definition, have no directly impacted soils. As a control, three additional soil samples will be collected at all 50 households during each of the six sampling time points in a section of the yard that is identified by the participant as unimpacted by failing sanitation. If no such area exists, then the researcher will randomly sample at three locations at the front, side, and back of the home. Once initially selected, the same household soil locations will be sampled at each of the six time points.

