## Limitations:

### Secular trends in exposures or outcomes

Because ITS analyses compare pre- and post-intervention trends of outcome measures, a limitation of this approach is the existence of non-intervention, secular changes that obscure or complicate the attribution of effects to the point of intervention. Additionally, an ITS does not include a control group; therefore, simultaneous trends may be incorrectly attributed to the intervention itself. Weather-related events, such as rainfall and temperature, are examples of independent variables that could act as potential confounders because extreme rainfall or temperatures can increase blockages and breakages in onsite wastewater treatment systems (37). We will closely monitor rainfall and adjust our analyses to account for any differences observed by incorporating comparison sites. However, it is important to note that the potential for residual confounding cannot be eliminated completely in this study design. As previously described, we plan to include a minimum of 10 comparison sites with existing adequate sanitation and 10 comparison sites with poor sanitation that will not be connected to the intervention until after this study concludes. This plan will allow estimates of (1) background levels of fecal microbes in sample matrices and (2) the influence of non-intervention-related factors (e.g., flooding) on the presence and quantity of sanitation-related microbes.

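### Equation 1 carries a two-group factor of 2, but its n of about 30 is used for a single pre/post series, so 30 households and 80% power do not go together on the plan's own equations

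*Protocol article*

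**What the plan says.** All references are to the protocol article.

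- **Sample Size Calculations.** The aim is a household count, with three visits before and three after connection, "to detect a meaningful change in soil *E. coli* concentrations with 80% power at a 5% significance level". The formula given for this, ahead of any clustering adjustment, is m = 2(z_α + z_Q)²σ²(1 − ρ₁)/(t s_x² d²), and the text reports m = 13. Equation 2 multiplies m by (1 + ρ₂)(k − 1) to reach about 30 "households needed to detect the specified effect size with 80% power at the 5% significance level". The section does not call m or n a number per group, and it mentions no comparison homes.
- **Data Analysis and Outcomes (Objective 1).** The primary regression estimates a step change and a change in slope from before to after the intervention.
- **Interrupted Time Series.** At least 10 homes with adequate sanitation are added, plus "10 more comparison households with poor sanitation that will not be connected to the intervention until after the conclusion of this study". They are to show background levels and influences unrelated to the intervention.
- **Secular trends in exposures or outcomes (Limitations).** An interrupted time series is said to have no control group, but the team will "adjust our analyses to account for any differences observed by incorporating comparison sites".
- **Soil Sample Collection.** "Impacted soil samples will not be collected at the 10 households with existing adequate sanitation services". Unimpacted yard soil is taken as a control at all 50 homes.

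**The concern.** The leading 2 and the analysis do not match. A coefficient estimated in one group of m households over t visits has variance σ²(1 − ρ₁)/(m t s_x²). Its sample size formula has no 2. The 2 appears when two such coefficients, from independent groups of m each, are subtracted. Equation 1 is therefore built like a per-group formula for two equal groups, yet its result serves as the whole connecting group in a single-series analysis.

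The comparison homes matter because the protocol relies on them to separate the sewer's effect from weather and other secular change. For impacted soil, only the 10 unconnected poor-sanitation homes are like for like, and their number does not enter the calculation. A reader who carries the 80% over to a comparison-adjusted result could take a null finding there as well powered evidence of no benefit.

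**Working it through.** **Inputs, all from Sample Size Calculations.** σ² = 5.2 (it "was calculated as 5.2 log (copies/gram)^2^ based on all available soil samples"), s_x² = 4.3, ρ₁ = 0.16, ρ₂ = 0.17, t = 6, k = 3, d = 0.45, 80% power, 5% significance. Sidedness is not stated.

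**Step 1: reproduce the plan.**
- Two-sided: (1.960 + 0.842)² = 7.849; σ²(1 − ρ₁) = 5.2 × 0.84 = 4.368; t s_x² d² = 6 × 4.3 × 0.2025 = 5.2245.
- m = 2 × 7.849 × 4.368/5.2245 = 13.12, printed as 13.
- Multiplier: 1.17 × 2 = 2.34. n = 13 × 2.34 = 30.4 (30.7 with m unrounded), printed as about 30.
- Without the 2: m = 6.56, n = 15.4. One-sided with the 2: m = 10.3, n = 24.2. Neither matches.

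The published numbers therefore need the factor 2 and a two-sided test.

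**Step 2: group sizes.** Overview of the Study Design gives 50 households, and 20 are comparison sites, leaving 30 to connect. The 30 is derived; the protocol does not state it in those words.

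**Step 3: power on the printed equations.** Variance per household V = 4.368/(6 × 4.3) × 2.34 = 0.396. Power = Φ(d/SE − 1.96).

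| Contrast | SE² | SE | d/SE | Power |
|---|---|---|---|---|
| 30 v 30 | V × 2/30 | 0.163 | 2.77 | 79% |
| 30 v 10 | V × (1/30 + 1/10) | 0.230 | 1.96 | 50% |
| One group of 30 | V × 1/30 | 0.115 | 3.92 | 97% |

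Only the first row agrees with the stated 80%, and it needs 30 unconnected homes.

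**Step 4: what does not depend on the other inputs.** (1/30 + 1/10)/(2/30) = 0.1333/0.0667 = 2. The variance doubles whatever σ², s_x² or the clustering multiplier may be, so the detectable difference rises by √2 ≈ 1.41. On the printed inputs, that takes it from about 0.45 to 0.64 log.

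**Step 5: how far the power figures depend on the other inputs.** The value put in for s_x² (4.3) is the within-household variance of the outcome. In a regression-coefficient formula that place belongs to the covariate. For a 3-before, 3-after indicator the covariate variance would be 0.25 (divisor 6) or 0.30 (divisor 5); this is my assumption. The usual design effect is 1 + ρ₂(k − 1) = 1.34, not 2.34.

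| Inputs | 30 v 30 | 30 v 10 | One group of 30 |
|---|---|---|---|
| As printed | 79% | 50% | 97% |
| Multiplier 1.34, s_x² = 4.3 | 96% | 73% | over 99% |
| s_x² = 0.25 to 0.30, no clustering factor | 17–20% | 11–12% | 30–35% |
| s_x² = 0.25 to 0.30, mean of three samples (variance × 1.34/3) | 33–39% | 19–22% | 58–66% |

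The loss from 30 v 30 to 30 v 10 is 29 points as printed, 22 with multiplier 1.34, and about 6 to 7 with s_x² = 0.25 and no clustering factor.

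**The case against.** **The protocol does not claim 80% for a comparison-adjusted effect.** This stands. The 80% is attached to households followed before and after connection, the primary contrast is pre/post, and the comparison sites have a supporting role. The effect d is described as due to the intervention, but no two-group contrast is named. A reader might infer that the plan promises 80% for the adjusted effect; the text does not say so. How the comparison sites enter the model may be left to an analysis plan that is not shown.

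**Per group is an inference.** This also stands. The protocol does not use the term, and the source it cites for the formula is not at hand. The inference rests on the algebra alone.

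**The 2 could come from subtracting before from after within a home.** This does not rescue it. With t/2 visits on each side, that difference has variance σ²(1 − ρ₁)(2/t + 2/t) = σ²(1 − ρ₁)/(t × 0.25). The before/after contrast is thus already contained in t s_x².

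**30 v 10 is not the whole design.** This stands. Connection is staggered, so homes not yet connected also inform time effects, and unimpacted soil is taken at every home and visit. The wording about a minimum number of comparison homes may also allow more than 10. A two-sample contrast ignores all of this.

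**The power figures rest on faulty inputs.** This stands, as Step 5 shows, and it limits how 50% and 97% may be used. It does not restore the pairing of 30 households with 80%.

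**Conclusion.** The point holds as a mismatch between formula and analysis. Equation 1 has the factor of a two-equal-group comparison, and the printed m and n depend on it. The protocol applies the result to one connecting series, and the comparison homes are absent from the calculation. On the plan's own equations, n = 30 with 80% power fits neither the single-series test (about 97%) nor a simple 30 v 10 contrast (about 50%).

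Two stronger conclusions are tempting and unsupported. One is that the study's true power is 50%. The other is that 15 homes would be enough, or that 30 give 97%. All of these keep s_x² = 4.3 and the multiplier 2.34, and the 50% also leaves out the staggered connection and the yard-soil controls. The only result free of the other inputs is that, in a plain two-group contrast, moving from 30 v 30 to 30 v 10 doubles the variance and makes the detectable difference about 1.4 times larger.

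The sample size section should be corrected. Confidence is medium, because the two-group reading rests on algebra and the cited source cannot be checked here.

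**What to change.** State in Sample Size Calculations which contrast the 80% covers, and recompute it with the factor that belongs to that contrast:

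- **Single-series coefficient:** replace 2/m by 1/m, and label the result as not adjusted for secular change.
- **Comparison-adjusted effect on impacted soil:** replace 2/m by 1/m₁ + 1/m₀, with m₁ = 30 and m₀ = 10.

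In the same recalculation, use the variance of the time or intervention covariate for s_x² and 1 + ρ₂(k − 1) for clustering. Say whether the variance refers to single samples or to the mean of three. Then print the power or the detectable difference for the 30 connecting and 10 comparison homes already planned.

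Do not simply delete the 2, and do not print 50%. Either would publish a new figure that carries the other two faults.

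The cost is one recalculation and some rewording, with no extra homes, visits or assays. The downside is that the stated power may become less favourable.

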### Eligibility and Enrollment

We will recruit households through public presentations at publicized community meetings, through the distribution of postcards via mail, door-to-door contact, and at a booth at the local farmer’s market. Recruitment material will include a description of this project, eligibility requirements, and how participants will be compensated for their time and knowledge. Eligible households will be located in the town or in neighboring, unincorporated communities. All households within the town limits will be eligible to be connected to the intervention. At least one person who is 19 years or older - the age of majority in Alabama - and resides at the enrolled household will act as a participant in the study and answer the survey questions. If the primary participant is unavailable at a given time point, another eligible household member may represent the household for that visit, as long as they meet the study requirements and undergo the informed consent process.

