### Research Objectives and Hypotheses

The evaluation team will examine the effects of the infrastructure project on environmental contamination, infection risk, and individual well-being. These elements are addressed in the following primary (Objective 1) and secondary (Objectives 2–4) research objectives:
Objective 1: Measure the density of fecal microbes (enteric pathogens and fecal indicators) released to the local environment at the household and community levels before and after the implementation of a community-wide sanitation system. Hypothesis: Community-wide sanitation will result in a reduction in the density of enteric pathogens and fecal indicators in the environment.Objective 2: Collect qualitative and quantitative data regarding the type and functionality of pre- and post-intervention sanitation infrastructure at the household level through participant-taken and observational surveys. Hypothesis: The community-wide sanitation system will result in a reduction in the prevalence of failing sanitation systems and straight-pipe discharge sites.Objective 3: Model the effects of the implementation of a community-wide sanitation system on the enteric infection risks associated with exposure to enteric pathogens and fecal indicators. Hypothesis: Community-wide sanitation will reduce infection risks associated with exposure to enteric pathogens and fecal indicators.Objective 4: Explore whether and how the changes in sanitation service affect the quality of life of the participants included in the study. Hypothesis: The intervention will improve the quality of life for participants.

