## Methods and analysis:

We will collect repeated environmental and household samples (wastewater, soil, drinking water, and surface water) across six structured time points to evaluate changes before and after intervention implementation, as outlined in Figure 1. All samples will be cultured for *E. coli*, and all soil, surface water, and wastewater samples will be analyzed for pre-specified enteric pathogens and fecal markers using quantitative PCR (qPCR). In addition to environmental sampling, structured surveys are conducted at selected time points: a demographic survey at time point one, sanitary inspection surveys at time points two and five, and a well-being survey at time points three and six (Figure 1). Further detail on survey content and analysis is provided in the detailed objectives below. The study began in August 2024 and will conclude at least three months after the final household in Phase II is connected to the intervention, currently targeted for December 2026. Each household follows the same six-point sampling schedule, although the exact dates vary depending on when the intervention reaches each home.

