### Well-Being Survey

We will collect data on participant well-being through a survey. The team will conduct surveys with a participant representing each of the 50 households enrolled in this study. The surveys will be conducted either in person or by phone at two time points, once before and once after the implementation of the community-wide sanitation system. These surveys will attempt to capture how limited access to sanitation services affects the overall well-being such as distress, fear of legal ramifications, and management related concerns. The surveys will be administered through Qualtrics (https://unc.az1.qualtrics.com/) through a combination of multiple-choice and open-ended questions. If the participant consents, the well-being survey will be recorded and transcribed. The outcome for Objective 4 is an assessment of changes in participants’ quality of life by comparing well-being before and after connection to the wastewater intervention.

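### The respondent-substitution rule does not exempt the well-being survey, so a household's single before/after contrast can compare two different people

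*Protocol article*

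**What the plan says.** The rule is in the protocol article, Eligibility and Enrollment. An adult who "resides at the enrolled household will act as a participant in the study and answer the survey questions" is the household's respondent. When that person cannot be present, "another eligible household member may represent the household for that visit". The substitute must be eligible and must consent; there are no other conditions. The rule is tied to the time point, not to the type of data collected there.

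The opening of Methods and analysis places "a well-being survey at time points three and six". The Well-Being Survey section under Objective 4 confirms that it is given "at two time points, once before and once after the implementation of the community-wide sanitation system". It may be done in person or by phone, with one participant representing each of the 50 households. The topics named are distress, fear of legal consequences, and concerns over managing sanitation. The outcome is a change in participants' quality of life, assessed by "comparing well-being before and after connection to the wastewater intervention".

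Research Objectives and Hypotheses introduces this strand as well-being at the level of the individual, and words Objective 4 as whether and how the change in service will "affect the quality of life of the participants included in the study". The abstract calls the survey a linked pre-post survey.

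**The concern.** For soil and water sampling, and for household facts such as where gray water goes, any informed adult resident will do. Distress and fear are different: one resident cannot report them for another. With one survey before connection and one after, a single change of respondent converts that household's entire contrast from within-person to between-person.

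Two things are at stake for Objective 4. Changes become noisier, because two members of a household usually agree less than one person does with herself. They may also be biased if substitution is lopsided, for example if the person most troubled by the sewage problem answers first and a less affected member answers later. This is a rule about data collection: once someone else has answered at time point six, no analysis can supply the first person's answer.

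**Working it through.** **The rule applied to the survey schedule.** The protocol states no figure to reproduce, so the first check is one of consistency.

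1. Substitution is allowed at any time point at which the primary participant is unavailable. Time points three and six are not excluded.
2. The Well-Being Survey section asks for a participant representing each household and does not require the same one twice.
3. Substitution at time points one, two, four or five has no effect here. It matters only when the person at three differs from the person at six.
4. The mismatch can arise from either side. Because substitution holds for one visit only, a substitute at three followed by the returning primary participant at six also gives a between-person contrast. If the same substitute answers both times, there is none.
5. The Bias section covers reporting, self-selection, courtesy and social desirability bias, but not a change of respondent.

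**Illustration of size, with assumed inputs.** Let f be the share of households whose respondent differs between the two surveys, r_w the within-person correlation and r_b the correlation between two members of one household. With equal variance at both surveys, in SD units:

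Var(change) = 2 × [1 − (1 − f) × r_w − f × r_b]

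Dividing by the value without substitution, 2 × (1 − r_w), gives the inflation if all pairs are kept. Using same-person pairs only multiplies the variance of the mean change by 1/(1 − f).

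| r_w | r_b | f | All pairs kept | Same-person pairs only |
|---|---|---|---|---|
| 0.5 | 0.3 | 0.2 | 0.54/0.50 = 1.08 | 1/0.8 = 1.25 |
| 0.5 | 0.3 | 0.3 | 0.56/0.50 = 1.12 | 1/0.7 = 1.43 |
| 0.7 | 0.3 | 0.2 | 0.38/0.30 = 1.27 | 1.25 |
| 0.7 | 0.3 | 0.3 | 0.42/0.30 = 1.40 | 1.43 |
| 0.7 | 0.2 | 0.2 | 0.40/0.30 = 1.33 | 1.25 |
| 0.7 | 0.2 | 0.3 | 0.45/0.30 = 1.50 | 1.43 |

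**Detectable change.** With a two-sided 5% test and 80% power, this is (1.96 + 0.84) × √(Var/N). Take r_w = 0.7 and r_b = 0.3.

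- N = 50 (all households): √(0.60/50) gives 0.31 SD with no substitution; √(0.76/50) gives 0.35 SD at f = 0.2.
- N = 30 (50 less the minimum of 20 comparison households in Interrupted Time Series): 0.40 SD with no substitution, 0.45 SD at f = 0.2 and 0.47 SD at f = 0.3.

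**Bias.** Let δ be the mean difference between substitute and primary respondent. Let p3 and p6 be the shares of homes with a substitute at time point three only and at six only. The shift in the mean change is (p6 − p3) × δ, so equal shares cancel. If all substitution falls at one survey, the shift is f × δ: from 0.2 × 0.2 = 0.04 SD to 0.3 × 0.5 = 0.15 SD for f of 0.2 to 0.3 and δ of 0.2 to 0.5 SD.

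**The case against.** The strongest reply is that this is a contingency on a minor objective. Substitution is open only when the primary participant is unavailable, and it cannot occur in a home with one eligible adult. Because the well-being survey may be done by phone, someone absent on sampling day can often still be reached, so mismatches may be rare. Objective 4 is secondary and worded as exploratory. The survey mixes multiple-choice and open-ended items, and the article names no scale, change score, test or power target. Some of the content, such as managing the system, is partly a household matter. Each substitute must consent, so the team should know when the respondent has changed. How mismatched pairs are analysed is commonly left to an analysis plan.

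Most of this stands, and it limits the size of the point. It does not remove it: allowing the phone is not the same as requiring the same person, and the enrolment rule as written permits the switch at both surveys that matter.

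A reader might go further and infer that the well-being comparison is biased, or that mismatched homes should be dropped from the main analysis. The documents support neither. They contain nothing on how often substitution occurs, at which survey, or how substitutes differ. The table shows that dropping pairs is a trade-off: variance rises by a factor of 1.25 to 1.43, against 1.08 to 1.50 if all are kept, and exclusion gains precision only towards the top of the assumed range. It could also select against homes whose first respondent is hard to reach.

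**Conclusion.** The point holds as a gap between a household-level substitution rule and an individual-level outcome measured once before and once after. Where the respondent differs between time points three and six, that household's change is partly a difference between two people. A variance increase of 8% to 50% and a shift of up to 0.15 SD are illustrations only; every input is assumed, and the shift also needs substitution to be one-sided. The consequence is confined to Objective 4. The primary soil *E. coli* outcome does not depend on who answers. The change is worth making because it is nearly free and must be made at data collection, not because serious harm has been shown.

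**What to change.** In Eligibility and Enrollment, limit the substitution rule to sampling visits and to surveys of household facts. In Well-Being Survey, require the team to seek the same respondent at time points three and six, by rescheduling or by phone, which that section already allows. Where time point three is already complete, the person to seek at six is whoever answered at three.

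If that person cannot be reached, a substitute may answer, with the respondent's identity recorded at each survey. Report the Objective 4 comparison both for all households and for same-respondent pairs, so that readers can see whether the change of respondent matters.

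The cost is a sentence or two of protocol text, a respondent identifier in the survey file, and a little more scheduling effort for some homes. No household need be lost from the comparison.
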